### Secondary analyses

The primary analysis will be repeated for 1) suicides, 2) suicide attempts, and 3) self-harm behavior. Number of events and person-time will be tabulated against timepoint and treatment arm.

Further key secondary endpoints are the EQ- 5D- 5L, the WHODAS 2.0 Short, DASS- 21 and the BSL- 23.

The EQ- 5D- 5L, BSL- 23 and the WHODAS 2.0 Short will be analyzed by time point using a linear mixed model with baseline value, treatment group, sex and age as explanatory variables. The randomization cluster will be considered as random effect. Missing values will be replaced using multiple imputation using FCS considering randomization cluster, sex, age and the respective value over time.

The DASS- 21 will be categorized. Ordinal regression will be used for analyses using the baseline category, sex, age, and treatment group as explanatory variables. Analyses will take place by time point. The randomization cluster will be considered as random effect. Missing values will be replaced using multiple imputation using FCS considering randomization cluster, sex, age and the value over time.

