### Primary outcome

#### Crisis events – composite outcome

The primary outcome of the study is the incidence of crisis events as indicated by 1) suicides, 2) suicide attempts, or 3) self-harm behavior.

To assess suicide attempts and self-harm behavior, the following four questions taken from the Self-Harm Behaviour Questionnaire ([53], German version: [54]) will be used: “Have you ever intentionally hurt yourself or caused yourself pain? (e.g. scratched with fingernails or with other sharp objects?)”, “How often have you intentionally hurt or caused yourself pain?”, “Have you ever tried to take your own life?” and “How often did you try to take your own life?”. These questions will be adapted for the Ecological Momentary Assessment (e.g., “Since the last signal have you ever intentionally hurt or caused yourself pain? (e.g., scratched with fingernails or with other sharp objects?”). Only if any of the crisis events occurred, the patient will be asked to indicate the frequency of the event(s).

Crisis events like suicides cannot be reported by the patient themselves but should be taken into account as well (see e.g. Bateman and Fonagy [18]). Suicides are recorded via the Serious Adverse Events (SAE) reports.

To increase ecological validity, the incidence of crisis events 1) – 4) will be assessed during one week each month over the course of 12 months of treatment, and one week every three months post treatment up to the 12-month-follow up (T3). During the assessment week, patients will be asked to complete one online-assessment every other day, resulting in 4 assessments per assessment week.

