### Primary analysis

The purpose of this trial is to show whether the (incidence) rate of crisis events (suicides, suicide attempts, self-harm behavior recorded throughout therapy and up to 12 month after therapy) is lower for BPD-patients undergoing MBT than for BPD-patients undergoing a BFT. The null-hypothesis (H01) to be tested can be formulated as follows: The (incidence) rates of crisis events in the MBT and in the BFT group are the same. A log-linear (Poisson) regression model (GLMM) will be used to fit with treatment group, sex and age as explanatory variables, along with log of observation (treatment + follow-up) time as an offset. The randomization cluster will be considered as random effect. Poisson regression lends itself to analysis of count data, considering that more events of suicidal behavior within a time frame are worse than one, and controlling for the period of observation by using it as an offset in the model. The null hypothesis (H01) of no treatment effect will be tested using Wald type tests on the regression coefficient of the treatment group (MBT vs. BFT). Tests will be two-sided at the 0.05 level.

Missing values will be replaced using multiple imputation using fully conditional specification methods (FCS) considering randomization cluster, sex, age and the respective value over time.

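### Suicides alone are to be analysed with the primary Poisson mixed model and Wald test, which gives no usable treatment estimate whenever one arm has no suicide

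*Protocol article*

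**What the plan says.** The article lists suicides as an individual secondary outcome (Crisis events—individually) and fixes the method under Secondary analyses: "The primary analysis will be repeated for 1) suicides, 2) suicide attempts, and 3) self-harm behavior". Event counts and person-time are also to be tabulated by time point and arm.

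The analysis to be repeated is defined under Primary analysis:
- **Model:** "A log-linear (Poisson) regression model (GLMM) will be used to fit with treatment group, sex and age as explanatory variables", with log observation time as an offset.
- **Clustering:** "The randomization cluster will be considered as random effect".
- **Test:** the null hypothesis "will be tested using Wald type tests on the regression coefficient of the treatment group"; "Tests will be two-sided at the 0.05 level".
- **Missing data:** multiple imputation by fully conditional specification, conditioning on cluster, sex, age and the same variable at other times.

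No exception is made for suicides. Their data source differs from that of the other two components, which come from patient questionnaires: "Suicides are recorded via the Serious Adverse Events (SAE) reports" (Crisis events – composite outcome).

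**The concern.** The model was chosen for a frequent, recurrent count. The article defends Poisson regression on the ground that several events in a period are worse than one, and it sizes the trial on 5 versus 3.75 events per patient. Neither applies to suicide, which a patient can contribute once and which probably only a handful of the 304 patients will.

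If an arm has no suicide, the log rate ratio is infinite and the Wald statistic collapses towards zero. The planned test would then report no evidence of a difference whatever the imbalance in deaths. The imputation step suits a questionnaire value repeated over time, not a single terminal event reported as an SAE. At stake is whether the stated analysis of the most serious component yields anything a reader can interpret.

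**Working it through.** **The plan's own figure.** The article states no expected number of suicides and no power for them. Its only figure for this model is 78% power for the composite. That is approximately reproduced with an effective size per arm of 152 × (1 − 0.3)² / (1 + 7 × 0.1) = 43.8. The standard error is √(1/(43.8 × 5) + 1/(43.8 × 3.75)) = 0.103, and |ln 0.75| / 0.103 = 2.79, which gives power 79.6%. Before dropout this rests on 152 × 5 + 152 × 3.75 = 1,330 expected events. It says nothing about suicides.

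**Expected suicides.** Inputs are 304 patients allocated 1:1 (152 per arm) and 24 months of follow-up (Aim, design and setting). The Background section gives 3–10% dying by suicide, without a time frame. The two-year risk is therefore an assumption. Spreading 3–10% evenly over an assumed 20 to 40 years gives between 304 × 0.03 × 2/40 = 0.5 and 304 × 0.10 × 2/20 = 3.0 suicides. If the whole 3–10% fell inside the trial there would be 9 to 30, an upper bound.

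**Chance of an empty arm.** With equal risks and λ = 152 × risk per arm, P(at least one arm has none) = 1 − (1 − e^−λ)²:

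| Assumed 2-year risk | Expected in total | λ per arm | At least one arm empty |
|---|---|---|---|
| 0.3% | 0.9 | 0.456 | 87% |
| 0.5% | 1.5 | 0.76 | 72% |
| 1% | 3.0 | 1.52 | 39% |
| 2% | 6.1 | 3.04 | 9% |

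At the lower bound of 9 suicides from the all-in-trial reading, the chance is 2%. The table assumes full observation. Simulated 30% dropout with shortened observation time raises the figure from about 40% to 45% at 3.0 expected, and from 10% to 16% at 6.0.

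**What the Wald test does then.** A Poisson regression on treatment alone, 304 patients, all suicides in the control arm:

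| Suicides (BFT vs MBT) | Log rate ratio | SE | Wald p | Exact two-sided p = 2 × 0.5ⁿ |
|---|---|---|---|---|
| 2 vs 0 | −20.4 | 11,459 | 0.999 | 0.50 |
| 4 vs 0 | −21.4 | 13,360 | 0.999 | 0.125 |
| 6 vs 0 | −22.4 | 17,985 | 0.999 | 0.031 |

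The coefficients are finite only because the iterations stop. At 5 versus 0 the exact p is 0.0625, so no exact test reaches 0.05 with fewer than 6 suicides.

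**A few suicides in both arms.** A 2:1 split gives an unadjusted rate ratio of 0.5 with SE √(1/2 + 1/1) = 1.22 on the log scale, so a 95% interval of 0.05 to 5.5. Using the same SE formula, power for a rate ratio of 0.75 is 3% to 5% across the table's range.

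**Imputation.** If a dropout's later suicide status were treated as missing, a simple rate-based stand-in for the imputation (30% dropout, 0.5 to 4.6 expected suicides) adds on average 0.2 to 0.6 suicides per completed data set. The article does not say whether that condition holds.

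**The case against.** Much of the opposing case stands.

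- **A usable report already exists.** Secondary analyses tabulates events and person-time by arm. Safety analyses tabulates SAEs as reported, with numbers and proportions of patients by arm. A reader might infer that the plan has no interpretable account of suicides; the text does not support that.
- **Few events do not always defeat the model.** A reader might infer that one to three suicides can never be fitted. That is too strong: a Poisson model with arm, sex and age, without the cluster term, converged on three simulated events split 2:1 and present in both sexes (log rate ratio −0.76, SE 1.23). Failure is certain only for patterns such as an empty arm.
- **Imputed suicides are possible, not stated.** A patient without a suicide report can be coded as zero, with the offset carrying observation time. The article does not give the coding rule, so it cannot be said that suicides would be imputed.
- **Decisions rarely change.** Among empty-arm outcomes, the exact and Wald tests disagree only at 6 or more versus 0. The probability, 2 × P(X ≥ 6) × e^−λ, is 0.001%, 0.01%, 0.2% and 0.8% at the four assumed risks.
- **The analysis plan may deal with it.** The article defers detail there, and a sparse-data rule for suicide attempts properly belongs there.

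The last argument does not dispose of the point for suicides. The article names the method for them, so an analysis plan that follows it inherits the problem and one that departs from it contradicts the published protocol. The tabulation limits the harm but does not withdraw the model, the Wald test or the imputation.

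**Conclusion.** The point holds as a badly chosen stated method for one component of a secondary analysis. At assumed two-year risks of 0.3% to 1%, the chance that the treatment coefficient cannot be estimated is 87% down to 39%; at 2% it is 9%. These figures rest on risks the documents do not give, equal rates in the arms, no clustering of suicides and full follow-up.

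The gain from changing it is an interpretable estimate in place of a meaningless one; a significance decision will seldom turn on it. On imputation the conclusion is limited: the text leaves room for it. A reader might also infer that the composite primary analysis is affected. It is not: it pools suicides with far more frequent events, and its power is untouched.

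**What to change.** Remove suicides from the repeated-model sentence, keeping it for suicide attempts and self-harm. Keep the planned tabulation and add, for example: *Suicides will be reported as observed SAE-reported counts and person-time by arm with exact Poisson 95% confidence intervals, without imputation; any exact conditional comparison of the arms is exploratory.*

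This stays computable in every case. With no suicide in an arm of 152 patients followed for two years (304 person-years), the upper limit is −ln(0.025)/304 = 1.2 per 100 person-years. At 0 versus 6 with equal person-time, the exact interval for the rate ratio runs from 0 to 0.85: the upper limit for the binomial share is 1 − 0.025^(1/6) = 0.459, and 0.459/0.541 = 0.85.

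The cost is a sentence or two and no new data. The suicide result loses the sex and age terms and also the cluster random effect, in a cluster-randomised trial planned with an ICC of 0.1. So few events could not support those terms, but the interval should be labelled as treating patients as independent.

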#### Depression, anxiety and stress scale – 21 items

The self-report Depression, Anxiety and Stress Scale – 21 Items (DASS- 21; [56], German version: [57]) will be used to assess emotional states of depression, anxiety and stress in the last seven days. Each of the three scales consists of seven items which are answered on a 4-point Likert scale (0 = “did not apply to me at all”; 3 = “applied to me very much or most of the time”). The score for each scale is quantified by adding up the scores of the items. The reliability of the scales is between *α* = 0.78 and *α* = 0.91 [57].

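### DASS-21, a key secondary endpoint, is categorised as outcome and as baseline covariate, which loses precision for no stated reason; the size of the loss cannot be derived from the protocol

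*Protocol article*

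**What the plan says.** The Secondary analyses section of the protocol article names four such endpoints: "Further key secondary endpoints are the EQ- 5D- 5L, the WHODAS 2.0 Short, DASS- 21 and the BSL- 23".

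For three of them (the WHODAS 2.0 Short, the EQ-5D-5L and the BSL-23), the rule is that the scores "will be analyzed by time point using a linear mixed model with baseline value, treatment group, sex and age as explanatory variables". A cluster random effect is included.

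The fourth is treated differently: "The DASS- 21 will be categorized. Ordinal regression will be used for analyses using the baseline category". This model also adjusts for age and sex, is fitted separately at each time point, and has a cluster random effect.

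The instrument section shows that a finer measure is available. On the DASS-21 it says: "Each of the three scales consists of seven items which are answered on a 4-point Likert scale", scored 0 to 3, and "The score for each scale is quantified by adding up the scores of the items". Each scale therefore runs from 0 to 7 × 3 = 21.

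The article gives no reason for banding the DASS-21 and describes no companion analysis of its scores.

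**The concern.** Cutting a 22-level score into a few ordered bands treats all patients within a band as equal. A patient who improves without crossing a cut-point counts as unchanged. Banding the baseline as well weakens the covariate adjustment, so less of the between-patient variation is removed.

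Both steps make the treatment comparison less precise. The protocol expects MBT to be superior on every secondary endpoint, and of the four key secondary scales the DASS-21 is the one described as measuring depression, anxiety and stress. A real difference on it would be harder to show than the collected data allow.

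Skewed or bounded scores do not require banding. A cumulative-logit model can be fitted to the ungrouped 22-level score without assuming normality.

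**Working it through.** **Figures in the document.** The protocol states no power, effect size, standard deviation, band count or cut-points for the DASS-21, so there is no figure of its own to reproduce. Its 78% power belongs to the primary Poisson analysis and has no bearing here.

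**Inputs from the document**
- Patients randomised in clusters of 8 (Aim, design and setting).
- Intraclass correlation (ICC) 0.1 and dropout 30% (Power calculations and sample size). Both are planning values for the primary endpoint; applying them to the DASS-21 is an assumption.

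**Assumed inputs**
- Five bands, with a share of 20% (equal bands), 50%, 60% or 70% in the top band and the rest split evenly over the other four.
- The same shares at baseline and follow-up.
- A normal baseline score, and a baseline-outcome correlation ρ of 0.5 to 0.6.

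**Step 1: outcome banding.** The efficiency of a proportional-odds analysis of grouped data, relative to the same model on the ungrouped score, is 1 − Σp³, where p is the share in each band.
- Equal bands: 1 − 5 × 0.2³ = 0.960
- 50% in top band: 1 − 0.5³ − 4 × 0.125³ = 0.867
- 60%: 1 − 0.6³ − 4 × 0.1³ = 0.780
- 70%: 1 − 0.7³ − 4 × 0.075³ = 0.655

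**Step 2: baseline banding.** The share R² of baseline-score variance kept by the category is 0.90, 0.79, 0.73 and 0.64 in the four scenarios. The precision factor is (1 − ρ²)/(1 − ρ²R²). For 70% in the top band and ρ = 0.6, it is 0.64/(1 − 0.36 × 0.64) = 0.83.

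**Step 3: patient-level efficiency.** E is the product of steps 1 and 2. For the example, 0.655 × 0.83 = 0.545.

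**Step 4: clustering.** Treatment is allocated by cluster, and banding adds noise only to the within-cluster part of the variance. The variance of a cluster mean is proportional to ICC + (1 − ICC)/(mE), where m is the cluster size. The loss is

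1 − [ICC + (1 − ICC)/m] / [ICC + (1 − ICC)/(mE)].

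With ICC 0.1, m = 8 and E = 0.545: 1 − 0.2125/(0.1 + 0.1125/0.545) = 1 − 0.2125/0.306 = 0.31.

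| Share in top band | E, patient level | Loss without clustering | Loss, 8 per cluster | Loss, 5.6 per cluster |
|---|---|---|---|---|
| 20% (equal) | 0.91-0.93 | 7-9% | 4-5% | 5-6% |
| 50% | 0.78-0.81 | 19-22% | 11-13% | 13-15% |
| 60% | 0.68-0.71 | 29-32% | 17-20% | 20-23% |
| 70% | 0.55-0.59 | 41-45% | 27-31% | 30-34% |

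The last column uses 8 × 0.7 = 5.6 patients per cluster after 30% dropout. With 8 per cluster, the standard error grows by 1/√(1 − loss): about 2-3%, 6-7% and 17-20% for top-band shares of 20%, 50% and 70%.

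**Checks**
- In a simulation of 38 clusters of 8 with only the outcome banded, clustering shrank the loss in the same way. From ICC 0 to ICC 0.1 it fell from 34% to 24% with 70% in the top band, and from 7% to 4% with equal bands.
- The loss does not depend on having exactly five bands. For a normal score with only the outcome banded, at patient level and against the ungrouped score, it is 36% with two categories, 19-21% with three, 8-10% with five and 4-7% with seven (optimal to equal cut-points). It shrinks with more bands but does not vanish.

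**The case against.** The strongest counter-argument is that banding is a legitimate choice of scale. A result in severity categories is easy to interpret, and ordinal regression on ordered categories is a valid test. The article defers detail to a statistical analysis plan, where cut-points and a supportive score analysis may well appear. This is one of several secondary endpoints, and the document claims no power for it.

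Most of this stands. The planned test is valid, missing cut-points are no fault in an article, and there is a real trade-off with interpretability. But the decision to band is made in the article itself, and no choice of cut-points removes the loss. Interpretability can be kept by tabulating the bands.

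A reader might also infer that the trial throws away 7-45% of the DASS-21 information, as if only about 280, 240 or 210 of 304 patients were analysed. The documents do not support that, for three reasons:
- Those figures treat patients as independent, whereas the trial randomises clusters of 8 and models the cluster.
- The upper end needs 60-70% of patients in the top band at follow-up. Recent self-harm or a suicide attempt at entry may suggest high baseline scores, but both arms then receive active psychotherapy. If patients improve, scores spread out and the loss moves towards the low end.
- The band count is itself assumed.

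Finally, multiplying an ordinal grouping efficiency by a linear-model covariate factor is an approximation. The results show order of magnitude only.

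**Conclusion.** The point holds as an avoidable loss of precision on a key secondary endpoint. The protocol fixes categorisation of the DASS-21 on both sides of the model, has the sum scores in hand, analyses the three comparable endpoints as scores, and gives no reason for the difference.

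The direction of the loss is certain; its size is not. With five assumed bands, ρ of 0.5-0.6, clusters of 8 and an ICC of 0.1 borrowed from the primary endpoint, it ranges from about 4-5% (equal bands) through 11-13% (half in the top band) to 27-31% (70% in the top band). The last scenario has no support in the document beyond the severity of the entry criteria.

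The planned analysis is not invalid, and nothing here touches the primary endpoint. It is a cheap improvement worth making.

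**What to change.** In Secondary analyses, or in the statistical analysis plan, replace the DASS-21 rule with two statements:

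1. Each of the three DASS-21 scale scores is analysed uncategorised, by time point, with its baseline score, treatment group, sex and age as explanatory variables and the randomization cluster as random effect. This is the linear mixed model already planned for the BSL-23 and WHODAS 2.0 Short.
2. Severity bands are reported descriptively by arm and time point, or the ordinal regression is kept as a supportive analysis.

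No new data are needed, and the planned multiple imputation can be applied to the scores. The downside is small: the main DASS-21 result becomes a difference in score points and no longer a comparison of severity bands. The change should be fixed before outcome data are analysed.

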## Safety analyses

### (Serious) adverse events (as reported)

Adverse events will be categorized by seriousness criteria, relatedness to study treatment and relatedness to study participation. Number of events, number and proportion of patients with at least one event will be tabulated against treatment arm.

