Mentalization-based treatment (MBT, [13]) has specifically been developed for the treatment of individuals with BPD. MBT is an integrative psychodynamic treatment rooted in attachment theory [14]. It assumes that mentalizing vulnerabilities lie at the core of the disorder. Mentalizing is the imaginative ability to interpret and understand the behaviour of oneself and of others in terms of mental states and develops in early attachment relationships [15]. Empirical research has shown that mentalizing is highly impaired in individuals with BPD especially with regard to emotionally intense relationships [14]. MBT follows distinct therapy rationales and is assumed to help alleviate BPD symptoms through inter alia improving mentalizing and epistemic trust, i.e. the trust in interpersonally transmitted information being relevant, trustworthy and generalizable for the individual [16]. MBT, alongside dialectical behaviour therapy (DBT; [17]), is the most studied psychotherapy for BPD. Five randomized-controlled trials (RCTs) have investigated the efficacy of MBT in BPD in comparison to psychiatric services [18], structured clinical services including supportive psychotherapy [19, 20], specialist BFT [21] and in adolescents with non-suicidal self-injury (NSSI) who mainly fulfilled criteria for BPD [22]. MBT proved to be superior to bona fide treatment (BFT)/clinical management in NSSI, suicide attempts, psychiatric symptoms, and hospitalization [18, 22] as well as core BPD symptoms [22, 23]. One RCT found MBT as effective as a specialist treatment-as-usual (TAU) for the primary outcome, reduction of Borderline symptom severity, with large effect sizes for both groups; however, there were significantly fewer drop-outs in the MBT group [21]. One independent RCT confirmed positive effects for MBT in comparison to supportive therapy for general functioning and BPD symptoms, suggesting that MBT may address core problems in BPD beyond NSSI and suicidality [20]. MBT is the only treatment for which superiority to clinical management was demonstrated in all primary outcome variables as well as a significantly higher level of employment or academic/occupation training eight years after randomization [24]. Findings also demonstrate that MBT shows superiority over TAU for interpersonal problems and general functioning [25]. In sum, MBT has demonstrated reliable improvements for psychiatric symptoms.

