## Methods/design

### Aim, design and setting

Based on the above-mentioned observations, we designed this cluster-randomized controlled trial (cRCT). It will be the first in Germany to investigate the efficacy of an outpatient MBT in comparison to BFT (here psychodynamic psychotherapy, PT, or cognitive-behavioural psychotherapy, CBT) for patients with BPD. BFT was chosen as a comparator for reasons of ecological validity. The primary objective of the RCT is to investigate whether MBT is more effective in the reduction of crisis events compared to BFT. Secondary, the trial will investigate whether MBT is superior to BFT with regard to cost-effectiveness, general and interpersonal functioning, BPD and psychiatric symptom severity, social adjustment, quality of life, changes in psychotropic medication and therapy retention. We expect that MBT will prove superior to BFT in all primary and secondary endpoints. We expect MBT to be more cost-effective for estimates on the financial burden of patients on society. Finally, while there are theories about and preliminary evidence for mechanisms of change [29], empirical validation of these mechanisms is lacking [30]. Thus, this trial will investigate moderator and mediator variables potentially associated with treatment outcome. Moderator variables are pre-treatment variables that predict treatment outcome in MBT and BFT (e.g. severity of BPD, treatment preferences, gender, trauma, initial level of mentalization and attachment). Mediator variables, i.e. the process of change, will be investigated comparing similarities and differences in change patterns between MBT and BFT. This is done by tracking changes of common and specific treatment factors in response to various stimuli. Common factors tracked are therapeutic alliance from both perspectives (patient and therapist) and both settings (individual and group) [31] as well as therapy related agency [32]. Specific factors are changes in mentalizing [33], epistemic trust [34], emotion regulation [35], attachment [36, 37], social pain (e. g. emotional reactions to rejection) [38], automatic thoughts [39], as well as therapist variables (treatment adherence and competence; [40, 41], and therapist-patient verbal and non-verbal interaction (attunement, [42]; rupture-resolution [43]).

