To investigate efficacy of MBT versus BFT, a total of *n* = 544 patients with a BPD diagnosis will be screened for eligibility at five study sites in Germany: University Hospital Heidelberg (Institute for Psychosocial Prevention, ST, and Department of General Psychiatry, SHe), University Hospital Jena (Institute for Psychosocial Medicine, Psychotherapy and Psychooncology, BS), University Hospital Düsseldorf (Clinic for Psychosomatic Medicine and Psychotherapy, UDE & JR), University Hospital Ulm (Clinic for Psychosomatic Medicine and Psychotherapy, HG, JV), Psychologische Hochschule Berlin (Department of Clinical Psychology and Psychotherapy, TS). Of the patients screened, *n* = 304 are expected to fulfil all inclusion criteria including informed consent to participate in the trial, to complete the baseline assessment (T0) and to be allocated to the trial (Fig. 1). Patients will be randomized in groups of 8 (randomization cluster) in a 1:1 ratio to either MBT or BFT using block randomization. Randomization will be stratified by study site. For randomization, study site coordinators will use a centralized web-based tool (randomizer.at) to maintain allocation concealment. Role-based user rights ensure that only approved study personnel may perform randomizations. Main assessments will be conducted for both arms at 6 months (in-therapy assessment, T1), at 12 months (T2) and at 24 months after start of therapy (12-months follow-up, T3). A final sample of *n* = 304 is expected to be obtained for data clearance and analysis using an intent-to-treat protocol. A drop-out of 30% during therapy is expected and acknowledged in our power analysis. Blinding of study team, trial personnel at site as well as patients is not feasible due to the nature of the interventions. Only central assessors will be blind to treatment. Allegiance bias is minimized as the consortium includes representatives of all trial treatments (MBT, group therapy, BFT).

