### Power calculations and sample size

In an RCT of MBT vs. structured clinical management (SCM), Bateman and Fonagy [19] encountered a mean count of 1.8 cases of critical behaviour in MBT vs. 2.6 cases in the SCM group at 12 months of treatment, resulting in a relative risk of 0.7. In another randomized controlled study of MBT vs. standard psychiatric care [18], the median count of self-mutilation in a 6-months period was reduced from 9 to 1 in MBT and from 8 to 6 in standard psychiatric care. As we expect our comparator to be more effective than the comparators used in the previous studies, we are raising the relative risk in order not to overestimate the effect of MBT. Accordingly, we assume 10 events per patient in the control group and 7.5 cases in the MBT group for the whole 24-months period, and would rate a relative risk of 0.75 [112] as sufficiently relevant requiring a model setting as described below to successfully reject the null hypothesis of no effect. As a more conservative approach, we assume less events (but the same relative risk), i.e. 5 events in the control group per patient and 3.75 in the treatment group. Therefore, a log-linear model (Poisson regression) with treatment as explanatory variable, and number of crisis events in 24 months as response, with a mean of 5 events expected for the BFT and 3.75 for the MBT group, results in a relative risk of 0.75. A test of the null hypothesis “no association between treatment and primary endpoint” at α = 0.05 level rejected with a power of 78% if 8 patients could be enrolled per cluster and 38 clusters could be randomized simulated with R assuming a dropout rate of r = 30% and an intraclass-correlation coefficient of 0.1 (ICC). The dropout rate is taken into account using the correction factor of 1/(1-r)^2 according to [113]. The sample size was corrected with help of the ICC according to [114].

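### The (S)AE table has no person-time, so if SAE observation shortens with drop-out and drop-out differs by arm, the better-retained arm would look less safe at equal risk

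*Protocol article*

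**What the plan says.** All references are to the protocol article.

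- **Safety analyses, (Serious) adverse events (as reported).** Events are categorised by seriousness and relatedness, and then: "Number of events, number and proportion of patients with at least one event will be tabulated against treatment arm". No person-time, rate or between-arm test is mentioned.
- **Secondary analyses.** For the individual crisis events: "Number of events and person-time will be tabulated against timepoint and treatment arm".
- **Primary analysis.** The Poisson model is fitted "along with log of observation (treatment + follow-up) time as an offset".
- **Aim, design and setting.** "A drop-out of 30% during therapy is expected and acknowledged in our power analysis". The secondary aims include "changes in psychotropic medication and therapy retention", and the stated expectation is: "We expect that MBT will prove superior to BFT in all primary and secondary endpoints".
- **Background.** Of one earlier RCT against a specialist comparator it reports that "there were significantly fewer drop-outs in the MBT group".
- **Participants.** Patients with an inpatient stay of more than 4 weeks during psychotherapy are taken out of the study and counted as drop-outs.
- **Serious adverse events.** SAEs are reported by study personnel, therapists or both. Inpatient hospitalisation is one of the seriousness criteria.

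**The concern.** A count of events, or a proportion of patients with at least one event, grows with the time over which patients are watched. The plan recognises this for crisis events, in both the primary model and the secondary tables, but the stated safety display does not carry it over.

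The document gives several reasons why SAE observation time could differ between arms. Drop-out is expected to be substantial. Therapy retention is expected to favour MBT. Therapists are among those who report SAEs, so a reporter may be lost when therapy stops. Some patients leave the study altogether after a long hospital stay.

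Readers will judge harm from this descriptive table. If the arms are watched for different lengths of time, it could suggest an excess of harm in the arm that kept its patients, or mask one in the arm that lost them.

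**Working it through.** **1. The plan's own figure.** The document states no SAE rate and no arm-specific retention, so there is no safety figure to reproduce. The nearest stated figure is the 78% power, which uses the same 30% drop-out.

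- Patients per arm: 38 × 8 / 2 = 152.
- Effective number per arm: 152 × (1 − 0.3)² / (1 + 7 × 0.1) = 152 × 0.49 / 1.7 = 43.8.
- SE of the log rate ratio: √[1/(43.8 × 5) + 1/(43.8 × 3.75)] = 0.103.
- |log 0.75| / SE = 0.288 / 0.103 = 2.79, and Φ(2.79 − 1.96) = 79.6%.

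This is close to 78%. The 30% is a single figure for both arms, and the present point does not affect the power.

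**2. Effect on the crude SAE figures at equal risk.** The following are assumptions, not document figures. The SAE rate λ is constant and the same in both arms. Drop-outs leave uniformly over year 1 and their later SAEs are not captured. All others are observed for 2 years.

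- Mean observed time with drop-out d: (1 − d) × 2 + d × 0.5.
- Proportion with at least one SAE: 1 − [(1 − d)·e^(−2λ) + d·(1 − e^(−λ))/λ].

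For λ = 0.3 per year, e^(−0.6) = 0.549 and (1 − e^(−0.3))/0.3 = 0.864.

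| Drop-out, MBT vs BFT | Mean years | Ratio of counts | Proportion with an SAE | Difference |
|---|---|---|---|---|
| 30% vs 30% | equal | 1.00 | equal | 0 |
| 25% vs 35% | 1.625 vs 1.475 | 1.10 | 37.2% vs 34.1% | 3.1 points |
| 20% vs 40% | 1.70 vs 1.40 | 1.21 | 38.8% vs 32.5% | 6.3 points |

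Each row averages the planned 30% overall.

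**3. What the added figures would show in the 20% vs 40% row.**

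- Person-years: 152 × 1.70 = 258.4 vs 152 × 1.40 = 212.8.
- Expected events: 0.3 × 258.4 = 77.5 vs 0.3 × 212.8 = 63.8.
- Events per person-year: 0.30 in both arms, ratio 1.00.
- Cumulative incidence of a first SAE by 24 months, under the same assumptions: 1 − e^(−0.6) = 45.1% in both arms.

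**4. A different loss model.** Suppose loss is exponential over 24 months with retention S. The mean observed time in years is then (1 − S)/(−ln S / 2).

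| 24-month retention, MBT vs BFT | Person-years | Ratio of counts | Proportions, rate 0.1 per year | Proportions, rate 0.4 per year |
|---|---|---|---|---|
| 75% vs 65% | 264 vs 247 | 1.07 | 15.8% vs 14.8% | 48.8% vs 46.0% |
| 80% vs 60% | 273 vs 238 | 1.15 | 16.3% vs 14.3% | 50.1% vs 44.6% |
| 85% vs 55% | 281 vs 229 | 1.23 | 16.8% vs 13.8% | 51.4% vs 43.1% |
| 65% vs 75% | 247 vs 264 | 0.93 | 14.8% vs 15.8% | 46.0% vs 48.8% |

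The mechanism does not depend on one drop-out model. The last row shows that it reverses if BFT retains better. Events per person-year give a ratio of 1.00 in every row.

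**5. Scale against chance.** With 152 per arm and a proportion near 36%, the SE of a difference, ignoring clustering, is √(2 × 0.36 × 0.64 / 152) = 5.5 points. The gaps of 3.1 and 6.3 points in step 2 are about 0.6 and 1.1 SE.

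**The case against.** The case on the other side is substantial.

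- **The display is standard and the article is a summary.** The article says that all analyses will be specified in a statistical analysis plan, which is not shown and may add rates. This stands as a caution. However, the safety section does state its display, and the section on secondary analyses states a better one for crisis events.
- **Therapy retention is not SAE observation time.** A reader might infer that MBT will look less safe. The documents do not support that. Assessments run to 24 months in both arms, analysis is by intention to treat, study personnel also report SAEs, and nothing says that SAE capture ends with therapy. The bias is conditional.
- **The direction is not fixed.** Under Procedure, BFT may be shorter or longer than MBT, so a reporting therapist could stay in contact longer in BFT. This stands. It removes any sure prediction of direction but not the need for a time denominator.
- **Rates have assumptions of their own.** They need a roughly constant hazard and uninformative drop-out. A patient removed after a long inpatient stay has probably just had an SAE, so a rate could overstate risk in the arm that loses more such patients. This stands, and it is why the crude figures should remain alongside.
- **No formal comparison is made.** The table is descriptive. A reader might also infer that the safety board would be misled, but the article does not describe the board's tables.
- **Part is already covered.** Suicides, suicide attempts and self-harm are analysed with observation time. Other SAEs, such as hospitalisations, are not.

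**Conclusion.** The stated (S)AE display lacks the time denominator that the plan uses for crisis events, although the plan foresees drop-out, removal from the study and a retention difference. The crude figures would mislead only if two conditions both hold: SAE observation shortens when patients drop out, and drop-out differs between arms. The size is modest and rests on assumed inputs. For drop-out gaps of 10 to 20 points around the planned 30%, it is about 10% to 21% in counts and, at 0.3 SAEs per year, 3 to 6 percentage points in proportions. It is nil if drop-out is equal or drop-outs are fully followed for SAEs, and it reverses if BFT retains better. The point concerns a better descriptive table. It does not show a wrong test or a predictable false alarm against MBT.

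**What to change.** In the section on (serious) adverse events:

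1. Keep the crude counts and proportions by arm.
2. Add person-years of SAE observation and events per person-year by arm, as the secondary analyses already do for crisis events.
3. Add the cumulative incidence of first SAE by arm.
4. Split the display into year 1 and year 2, since MBT ends at month 12.
5. State that SAE observation time runs to last contact for patients who stop therapy or are removed after a long inpatient stay.
6. Note that the rates assume a roughly constant hazard and uninformative drop-out, and are to be read beside the crude figures.

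The cost is one extra descriptive table or figure, built from dates of randomisation, SAE and last contact that the trial needs anyway.
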